## Abstract

**Background:**

The 360° fusion of lumbar segments is a common and well-researched therapy to treat various diseases of the spine. But it changes the biomechanics of the spine and may cause adjacent segment disease (ASD). Among the many techniques developed to avoid this complication, one appears promising. It combines a rigid fusion with a flexible pedicle screw system (hybrid instrumentation, “topping off”). However, its clinical significance is still uncertain due to the lack of conclusive data.

**Methods/Design:**

The study is a randomized, therapy-controlled, two-centre trial conducted in a clinical setting at two university hospitals. If they meet the criteria, outpatients presenting with degenerative disc disease, facet joint arthrosis or spondylolisthesis will be included in the study and randomized into two groups: a control group undergoing conventional fusion surgery (PLIF - posterior lumbar intervertebral fusion), and an intervention group undergoing fusion surgery using a new flexible pedicle screw system (PLIF + “topping off”), which was brought on the market in 2013.

Follow-up examination will take place immediately after surgery, after 6 weeks and after 6, 12, 24 and 36 months. An ongoing assessment will be performed every year.

Outcome measurements will include quality of life and pain assessments using validated questionnaires (ODI - Ostwestry Disability Index, SF-36™ - Short Form Health Survey 36, COMI - Core Outcome Measure Index). In addition, clinical and radiologic ASD, sagittal balance parameters and duration of work disability will be assessed. Inpatient and 6-month mortality, surgery-related data (e.g., intraoperative complications, blood loss, length of incision, surgical duration), postoperative complications (e.g. implant failure), adverse events, and serious adverse events will be monitored and documented throughout the study.

**Discussion:**

New hybrid “topping off” systems might improve the outcome of lumbar spine fusion. But to date, there is a serious lack of and a great need of convincing data on safety or efficacy, including benefits and harms to the patients, of these systems. Health care providers are particularly interested in such data as these implants are much more expensive than conventional implants. In such a case, randomized clinical trials are the best way to evaluate benefits and risks.

**Trial registration:**

NCT01852526

## Background

Lumbar spine fusion is a controversial surgery. While some evidence suggests that it could be more efficient than commonly used nonsurgical treatment, there is also evidence to the contrary [1]. But in spite of the inconclusive results, it remains a well-established and frequently used surgical treatment for various diseases of the lumbar spine and chronic low back pain.

Spinal fusion is known to change the biomechanics of the spine, e.g. it can result in increased motion in the segments adjacent to the fused level. Outweighing the initial clinical benefits from the surgery, this motion may cause adjacent segment disease (ASD) that is defined as the clinical presence of symptoms which correlates to degenerative disease adjacent to the index level with the radiographic presence of disease. It must be distinguished from adjacent segment degeneration, a radiological term that does not lead to clinical symptoms [2].

Thus different techniques (disc arthroplasty and dynamic stabilization) have been developed to prevent this degeneration [3]. In this context, the posterior dynamic stabilization (PDS) is one of the most rapidly evolving technique, including various types of flexible pedicle screw systems, such as the “topping off” version mentioned above. Other PDS devices include interspinous spacers used by some surgeons together with a monosegmental rigid fusion [4]. To simplify the discussion of these devices, Khoueir et al. [5] classified them into:Interspinous spacer devices;Pedicle screw/rod-based devices; andTotal facet replacement systems.

The concept behind these devices is to maintain or restore intervertebral motion in a controlled manner, whether by preventing excessive spinal movement or by dampening the kinetic energy. They are designed to mimic the behaviour of the healthy spinal column [5, 6]. Various types of flexible pedicle screw systems (e.g. Dynesis™, DSS™, cosmicMIA™) and “topping off” systems (e.g. DTO™, BalanC™,) have been developed.

The ”topping off” technique has been reported to provide dynamic stabilization and to reduce degeneration in the adjacent segment [7, 8]. Some studies report better clinical outcomes in patients with partial fusion than with solid fusion, they suggest that reducing, rather than eliminating, segmental motion alleviates pain. It could be a promising alternative to multilevel fusion [9] and, according to Coe et al., to rigid fusion [10].

One of the most extensively used posterior dynamic stabilization systems is Dynesys®, in which pedicle screws are connected across spinal motion segments with non-elastic bands to provide controlled motion. In early clinical outcomes, it has been shown to lessen pain and disability in patients with degenerative spondylolisthesis and central or lateral spinal canal stenosis. Comparable clinical outcomes of other pedicle-based dynamic stabilization systems have also been reported [11, 12]. However, in a prospective, randomized clinical trial of 60 patients comparing hybrid with conventional fusion over 6 years of follow-up, clinical results did not differ between the groups (ODI, VAS, satisfaction). Hybrid fixation caused less degeneration in the adjacent segment, but showed a higher rate of implant failure. This study group did not recommend prophylactic dynamic stabilization [13].

In patients with lumbar spinal stenosis that underwent decompression and stabilization with the Accuflex™ dynamic system, Reyes-Sánchez et al. report a relatively high hardware failure (22%), but also clinical benefits and cessation of the degenerative process in 83% of the patients [11].

As a summary, it can be said that there is still no evidence of any clinical benefit from these systems.

Another issue is whether the radiographically detectable adjacent degeneration is an indicator of clinical outcome. As already mentioned, spinal fusion creates increased strain on adjacent levels and can result in ASD. Adjacent instability has been reported even 6 to 12 months after surgery [3, 14], with varying average rates. In a retrospective study, Cheh et al. identified radiographic ASD in 42.6% of the patients (average follow-up of 7.8 years). Oswestry scores were worse in patients with radiographic ASD. Clinical ASD developed in 43% [3]. Other authors reported an incidence of ASD of up to 24% (average follow-up of 39 months). In that study, instability developed more frequently above the fusion [14]. Yang et al. found a significant correlation between clinical outcome and ASD [15]. In a 30-year follow-up comparing patients undergoing various spinal procedures (fusion, discectomy, decompression), Kumar et al. [16] found that the incidence of radiographic changes in levels above the operated region was twice higher after fusion than after the other procedures. In contrast, validated scales and functional testing (e.g. SF-36) showed no significant differences in outcome. The authors concluded that radiographic changes do not necessarily lead to functional impairment in all patients. Other evidence suggests that radiologic degeneration of the superior adjacent segment does not correlate with clinical results [17]. Ghiselli et al. reported an adjacent segment disease rate of 16.5% after 5 years in a collective of 215 patients who had undergone lumbar spine arthrodesis. This rate went up to 30.1% at ten years follow-up [18]. However, a previous review mentions a correlation between fusion and adjacent segment degeneration compared to arthroplasty. This correlation appears to be even stronger if adjacent segment disease is observed, thus underlining the impact of fusion on the adjacent segments [2]. In this context, sagittal imbalance is another factor of considerable importance; some studies indicate that it favours the development of the disease [19, 20].

### Objective

The objective of the study is to address the following questions:

Does posterior hybrid stabilization with a new topping off device lead to a better or at least equivalent clinical outcome compared to standard fusion? Clinical outcome assessment will be performed using ODI, SF-36 and COMI questionnaires.

Does it prevent adjacent instability/segment disease?

Does radiographic ASD correlate with clinical outcome?

Does this new device lead to a higher complication rate (e.g. implant failure) than standard fusion?

## Methods and design

The study is a randomized, parallel-group, therapy-controlled trial in a clinical setting at two university hospitals. Outpatients presenting with degenerative disc disease, symptomatic facet joint arthrosis or spondylolisthesis will be assessed for inclusion. They will be asked to give an informed consent and will be randomized before surgery. Follow-up examinations will take place immediately after surgery, and after 6 weeks, 3 months and 6 months, the total duration of the study. Furthermore data will be assessed after 12, 24 and 36 months for a supplemental investigation. A further assessment will be performed every year, as it may be impossible to pronounce on ASD after 36 months.

This trial has received the approval of the ethics committee of the medical faculty of the University of Cologne under the reference number 12–231. The Clinical Trial Centre of the University of Cologne will monitor and manage the data. The research will be carried out in compliance with the Helsinki Declaration [21].

### Participants and recruitment

Outpatients over 30 years of age presenting with degenerative disc disease, facet joint arthrosis or spondylolisthesis, and indications for monosegmental lumbar spine fusion will be eligible for trial inclusion. Radiologic inclusion criteria are summarized in the Appendix.

The presence of radiologic degeneration of the adjacent segment (Pfirrmann grades II-IV in MRI findings [22]) without signs of instability will be a condition for inclusion. The definition of radiologic and clinical instability and the other inclusion criteria are summarized in the Appendix.

Experienced spine surgeons will approach and recruit the study subjects. The number of patients who undergo primary monosegmental fusion in the departments is estimated at 200 per year and the number of recruited patients at 20 per year per centre.

Patients participating in parallel interventional studies as well as patients with lumbar scoliosis (>25° cobb angle), spondylolisthesis Meyerding IV, adjacent segment instability and/or radiologic ASD worse than Fujiwara grade II or Pfirrmann grade IV [22, 23] will be excluded from this study. This also applies to patients with indication for multilevel fusion. The other exclusion criteria are summarized in the Appendix.

### Interventions

#### Patients will receive one of two treatments

Monosegmental posterior lumbar intervertebral fusion (PLIF)Hybrid system (PLIF + flexible pedicle screw system above the fusion)

#### Control group - conventional PLIF

The control group will be treated with a conventional, monosegmental posterior lumbar spine fusion with a rigid pedicle-based instrumentation and posterior intervertebral cages (PLIF), the current well-established therapy for several pathologies of the lumbar spine (see Appendix under “Inclusion Criteria”). Thus, the control group will receive the standard of care. This is the only acceptable control/comparison in a trial of this kind. Surgery will be performed using the following devices: S^4^® AESCULAP AG, Cage: Wave® Cage (Fa. Medtronic®).

#### Intervention group - hybrid system

The intervention group will be treated with a hybrid system with PLIF (rigid pedicle-based instrumentation and posterior intervertebral cages) and a flexible pedicle screw system above the fusion. Surgery will be performed using the following devices: S^4^® Dynamic rod (AESCULAP AG, Tuttlingen), Wave® Cage, (Fa. Medtronic ®). The dynamic connecting rod of the S4 Spinal System is used for the dynamic monosegmental stabilization through the dorsal approach and the fusion of one or two adjacent segments. It consists of a spring element, a short rod section on one side, and another rod section that varies in length on the other side. The materials used in the implant are pure titanium and titanium forged alloy Ti6Al4V. The prototype of this dynamic implant has already been biomechanically tested and compared with other dynamic devices and a rigid one; no significant ROM reduction (extension, flexion, lateral bending) was detected. In addition, the implant brought about a significant reduction of axial rotation [24].

### Surgery and treatment

Only skilled spine surgeons (experience of at least 30 fusions-procedures/per year) will participate in the trial. To avoid variations in surgical procedure (e.g. size of decompression/approach), intraoperative photos and an instructional video on the standards of the procedure will be provided to the surgeons. In both groups, autologous bone spongiosa, harvested during the decompression procedure, will be implanted in the intervertebral disc space with the intervertebral cages.

The patients will have the surgical drain removed 2 days after surgery. Beginning on the day after surgery, both groups will receive physical therapy. Patients will be discharged only after appropriate recovery if wound healing is progressing normally. They will remain in the hospital for 8–10 days. After hospital discharge, they will continue to receive physical therapy as outpatients, but not in standardized form to reproduce real conditions.

### Outcome measures and assessments

#### Primary outcome measures

This investigation focusses on the subjective and objective clinical benefits for the patient. The ODI scores will be used to evaluate the functional outcomes after 6 weeks and after 6, 12, 24 and 36 months after surgery. The study hypothesis is:

The improvement in ODI scores from baseline to 6 months after surgery is clinically superior in the group with D-Rod (μRod) compared with the group without D-rod (μ).

To prove it, the following null hypothesis must be rejected: H0: |μRod - μ| ≤ MCID;

The alternative hypothesis is: H1: |μRod - μ| > MCID, with MCID assigning for minimum clinically important difference.

The hypothesis will be tested using a two-sided t-test for independent samples with a significance level of 5%.

In accordance with the recommendations of the European Agency for the Evaluation of Medicinal Products (EMEA), the patient’s bodily function may not be impaired if the only medical benefit is to relieve pain [25].

The ODI (cross-cultural adaption of the ODI version 2.1 for use with German-speaking patients) is a standardized, condition-specific questionnaire that gives a subjective percentage score of level of function (disability) in 10 everyday activities of daily living to be completed by patients rehabilitating from low back pain [25].

In the past, spine surgery investigations have focused on technical outcomes; now the main interest has turned to clinical outcomes [26, 27], measured by the ODI and SF-36™ , as in recent important trials (RCTs) [28, 29]. Radiologic findings are poor indicators of clinical outcome as it is unclear whether they correlate with clinical success.

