
### Sample size

On the basis of the data provided by Parker et al., the standard deviation is set at 11.3 points and the minimal clinically relevant difference at 11 for the changes in the Oswestry Disability Index (ODI) scores between the baseline and six months. In order to detect this clinically relevant difference between the two treatment groups, using a two-sided t-test with a significance level of 5% and a power of 80%, a total of 36 patients is required (18 per group) [30].

Assuming a drop-out rate of 10% until follow-up, 40 patients must be recruited for the study.

At a recruitment rate of 50% of the eligible patients and a rate of 60% of eligible patients in the screened population, 80 patients must be eligible among the 133 screened patients.

At a screening rate of approx. 100 patients in 12 months, duration of recruitment would be 16 months. To comply with the CONSORT requirements, we will provide a flow diagram of the participants. For each group, it will show the numbers of participants who were randomly assigned, received intended treatment, and were analysed for the primary outcome. Furthermore a diagram will illustrate for each group, losses and exclusions after randomization, together with reasons [31].

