### Data analysis

#### Primary target variable

The primary target variable is the functional change in the lumbar spine between baseline and 6 months as measured by the Oswestry Disability Index (ODI). The two-sided t-test for independent samples will be used as confirmatory test to compare the intervention group with the control group.

Analysis will be based on the intention-to-treat (ITT) principle. Consistency of the results will be verified by additional per-protocol (PP) subgroup analysis.

In addition, the results will be evaluated, focusing separately on each of the three diseases: degenerative disc disease, degenerative spondylolisthesis und spondylolisthesis. This applies to both the results from the ODI and to all other secondary target variables.

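### The primary hypotheses ask for a difference beyond the MCID, but the t-test and the 36 patients address a difference from zero

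*Protocol article*

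**What the plan says.** Three places in the protocol article bear on the primary comparison.

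- **Primary outcome measures.** The study hypothesis is directional: "The improvement in ODI scores from baseline to 6 months after surgery is clinically superior in the group with D-Rod". The route to it is explicit: "To prove it, the following null hypothesis must be rejected: H0: |μRod - μ| ≤ MCID". The alternative is "H1: |μRod - μ| > MCID", "with MCID assigning for minimum clinically important difference". The test is then named: "The hypothesis will be tested using a two-sided t-test for independent samples with a significance level of 5" percent. The section gives neither a null value for that test nor a number for the MCID.
- **Sample size.** The SD of the ODI change is set at 11.3 and the minimal clinically relevant difference at 11. The purpose is stated as: "In order to detect this clinically relevant difference between the two treatment groups, using a two-sided t-test with a significance level of 5" percent, with 80% power. The result is 18 per group (36 in all), raised to 40 for 10% drop-out.
- **Data analysis, Primary target variable.** "The two-sided t-test for independent samples will be used as confirmatory test to compare the intervention group with the control group". The MCID is not mentioned.

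**The concern.** A true difference of exactly 11 lies inside the written null. A valid 5% test of that null rejects there at most 5% of the time, whatever the sample size, so it cannot have the 80% power that the Sample size section plans for. Either the hypotheses or the sizing must be wrong.

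The conclusion of the trial depends on which it is. A significant t-test against zero shows that the groups differ. It does not show that they differ by more than a clinically important amount. A reader who follows the Primary outcome measures section literally would take a significant result as proof of the second statement. The Discussion section says that these costlier systems should be used only if they bring a worthwhile benefit, so the distinction matters.

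There is also a directional fault. The claim is superiority of the D-Rod, but the alternative is written with an absolute value, so a D-Rod group worse by more than the MCID satisfies it too. The Discussion itself allows that the larger surgical approach could worsen outcome.

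**Working it through.** **Inputs (Sample size section).** SD 11.3; difference to detect 11; two-sided α 0.05; power 80%; 18 per group; drop-out 10%. I take the 11-point minimal clinically relevant difference to be the MCID of the hypotheses.

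**1. Reproducing the plan's figure.** Null of zero, non-central t:

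- SE = 11.3 × √(2/18) = 3.767
- Non-centrality at 11 = 11 / 3.767 = 2.92, with 34 df
- Power = 78.6% at 17 per group and 81.0% at 18 per group
- 36 / (1 − 0.10) = 40

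The stated 36 and 40 are therefore correct for a test of zero difference.

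**2. What that test needs to be significant.** t(0.975, 34) = 2.032, and 2.032 × 3.767 = 7.65. With an observed SD of 11.3, an observed difference of about 7.65 points is enough, which is 3.35 points short of 11.

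**3. Reading significance as rejection of the written null.** All the true differences below lie inside that null. The rate is the probability of a significant result favouring D-Rod at 18 per group.

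| True difference | Rate |
|---|---|
| 0 | 2.5% |
| 4 | 18% |
| 7 | 44% |
| 9 | 64% |
| 11 (boundary) | 81% |

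**4. Testing the written null instead.** There are two conventions, both at 18 per group.

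| | 5%-level test of the composite null | Lower 95% limit must exceed 11 |
|---|---|---|
| Critical t, 34 df | 1.691 | 2.032 |
| Observed difference needed | 11 + 1.691 × 3.767 = 17.37 | 11 + 2.032 × 3.767 = 18.65 |
| Power at a true 11 | 5% | 2.5% |
| True difference for 80% power | about 20.6 | about 21.9 |
| Per group for 80% power at a true 15 | 100 | 127 |

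In the first convention, only one tail contributes at the boundary of the composite null; the other is about 10⁻¹³. The critical value is therefore the one-sided 5% point. The second convention is directional, with 0.025 in the upper tail. The documents give no true difference above 11, so 15, 20.6 and 21.9 only illustrate the scale.

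**The case against.** **The 81% is only the planned power under another name.** A reader might infer that the trial would falsely claim clinical superiority 81% of the time. The documents do not support that. The figure is the maximum over the written null and occurs only at a true difference of exactly 11. The Sample size section itself regards 11 as clinically relevant, and 11 falls inside the null only because the inequality is written as ≤ and not <. At smaller true differences the rate is lower, as the table shows. It also arises only if a significant zero-null test is reported as rejecting the MCID null. This objection stands, and the 81% should be quoted only as a ceiling with those conditions.

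**The text never says that the t-test is against zero.** True: neither section that names the test gives a null value, and a t-test shifted by the MCID is possible on the wording alone. The zero null is inferred from the sizing. A shifted test would not remove the contradiction, because 36 patients would then have 2.5% to 5% power at the planning effect. An analysis plan that is not shown could therefore rescue one section only at the expense of the other.

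**The fault is confined to the hypothesis lines.** Also true. Endpoint, time point, sample size and confirmatory comparison agree with one another, and the sample size arithmetic is sound. But those lines define what the trial may claim, so the fault is more than loose notation.

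**Conclusion.** The point holds as a mismatch between the stated hypotheses on one side and the sizing, with the test it implies, on the other. It is wrong as written. The 36 patients fit a test of zero difference (81% power at 11). They do not fit the null that the protocol says must be rejected, for which power at 11 is 5% or 2.5% depending on the convention. The implied test can be significant from about 7.65 observed points, so significance alone cannot carry the claim that improvement "is clinically superior in the group with D-Rod" by more than the MCID. The absolute-value alternative separately contradicts the direction of the claim.

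The figures rest on SD 11.3, 18 evaluable patients per group, equal variances, and the 11 points of the Sample size section being the MCID of the hypotheses. The contradiction does not depend on the SD, because a true difference equal to the margin always lies inside the written null.

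**What to change.** Amend the Primary outcome measures section to agree with the Sample size and Primary target variable sections:

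- State H0: difference in mean ODI improvement (D-Rod minus control, baseline to 6 months) = 0, and H1: difference ≠ 0.
- Conclude superiority only if the test is significant and the difference favours D-Rod.
- State that 11 is the difference to detect and that the 80% power refers to the zero-difference null.
- Report the 95% CI against 11 points, and say that a significant t-test alone is not proof of benefit beyond the MCID.

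**Cost.** No added patients, visits or measurements. This is nevertheless more than an edit of wording, because it changes the confirmatory hypothesis and makes the formal claim less ambitious: superiority, and no longer superiority by more than the MCID. Keeping the stronger claim would mean justifying a true difference well above 11 and re-sizing the trial. At an assumed true 15, that would be 100 or 127 evaluable patients per group under the two conventions, against the planned 18.
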